### Patient inclusion and exclusion criteria

The inclusion criteria of the participants will be: (1) diagnosed as having a unilateral stroke, (2) 1 to 6 months after stroke onset, (3) from 20 to 80 years of age, (4) a baseline score of the Fugl-Meyer Assessment (FMA) of 20 to 60 [28], (5) able to follow the study instructions (measured by the Taiwan version of the Montreal Cognitive Assessment) [29], and (6) capable of participating in therapy and assessment sessions. The exclusion criteria will be: (1) global or receptive aphasia, (2) severe neglect, and (3) major medical problems or comorbidities that influenced UE usage or cause severe pain.

In addition, if patients have no metal implants, no head traumas or neurosurgical operations, and can perform MEG motor tasks, they can additionally participate in the MEG assessment. For the MEG portion of the study, we expect to recruit 12 to 15 patients in each group. Patients can still participate in the study, receiving rehabilitation therapy and clinical evaluations, even if they do not meet the MEG eligibility criteria, or are not willing to participate in the MEG study. All participants must provide written informed consent before entering the study.

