#### Primary outcomes

The upper-limb subscale of the FMA will be used to evaluate motor impairments [28]. The 33 items assess movements, reflexes, and coordination of the shoulder, elbow, forearm, wrist, and hand. The total score ranges from 0 to 66, with a higher score indicating less motor deficit. The psychometric properties of the FMA have been well established in patients with stroke [31].

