#### Secondary outcomes

The mRS will be used to assess the degree of stroke disability in this study. The mRS was found to be valid and reliable in stroke patients [32]. The mRS scores range from 0 to 5. Higher scores indicate more severe disability. Favorable outcomes of patients are defined as the mRS score of ≤ 2 which indicates no or slight disability [33].

The BBT is a measure of hand dexterity with satisfactory reliability and validity in patients with stroke [34, 35]. The BBT to be used in this study contains 150 colored wooden cubes in a box with two compartments. The participants will be instructed to use their affected hand to move as many blocks as possible one-by-one from one compartment to the other within 1 min. The number of blocks transferred by the affected hand is counted as the score of the BBT.

The ABILHAND questionnaire is self-reported and assesses patients’ perceived difficulty in performing daily activities that require the use of bilateral UE [36]. It contains 23 daily activities measuring bimanual ability and is rated on a 3-point scale (0 = impossible, 1 = difficult, 2 = easy). Its psychometric properties have been validated in patients with stroke [37].

The short-form of the QMI will be applied to assess the ability of the patient’s mental imagery. The 35-item questionnaire consists of seven domains of sensory modalities [38]. The score of each item ranges from 1 (perfectly clear) to 7 (no image present at all). A lower score indicates better mental imagery ability. The test-retest reliability of QMI has been validated [39].

The FIM is a scale frequently used to assess basic activities of daily function. It consists of 18 items with a total score ranging from 0 to 126 [40]. The FIM includes six subscales: self-care, sphincter control, transfer, locomotion, communication, and social cognition ability. A higher score indicates less disability for basic daily function. The FIM is an assessment with good reliability, validity, and responsiveness [41, 42].

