The ActiGraph GT3X^+^ accelerometers (ActiGraph, Pensacola, FL, USA) will be used to provide an objective measure of the amount of using the affected arm in the patients’ real-life environments [43]. The participants will wear the accelerometers on each wrist for three consecutive days before and after treatment. The main outcome parameters will be the amount of physical activity (counts/min), activity intensity, and energy expenditure in real life. The accelerometer-based devices are commonly used to monitor physical activity in stroke patients [44].

The SIS version 3.0 is a patient-reported outcome to evaluate function, participation, and health-related quality of life of stroke survivors with sound psychometric properties [45]. It consists of 59 items, with a higher score indicating better function and greater participation.

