### Data analysis

An intention-to-treat analysis will be performed. Two-way repeated measures analysis of variance (ANOVA) will be used to evaluate the treatment effects among the three treatment groups at the three assessments from different time points. The between-subject factor will be the group and the within-subject factor will be the time. The treatment efficacy will also be examined by determining the number of participants whose change score reaches the minimal clinically important difference (MCID) in the clinical outcomes, by using a chi-square test. The MCID values will be adopted either for the established values of outcomes or 10% of the total scores when it has not been established. A *p* value < 0.05 will be considered as indicating statistical significance.

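### The fallback MCID of one tenth of the total score cannot be applied as written to every listed outcome, yet it feeds a chi-square test of efficacy

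*Protocol article*

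**What the plan says.** In the Protocol article, Data analysis names a two-way repeated-measures ANOVA (group by time) first and then adds a responder analysis: "The treatment efficacy will also be examined by determining the number of participants whose change score reaches the minimal clinically important difference (MCID"). The groups are to be compared on these counts by chi-square, for the clinical outcomes generally. The cut-offs are to be taken "either for the established values of outcomes or 10% of the total scores when it has not been established". One significance threshold, p < 0.05, is given for the whole section. No MCID value is stated for any outcome, and the outcomes expected to need the fallback are not named.

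Outcome measures lists the FMA as primary. The secondary clinical outcomes are the mRS, BBT, ABILHAND, Questionnaire Upon Mental Imagery (QMI), Functional Independence Measure (FIM), activity monitors and SIS. The scale descriptions that matter here are:

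- FMA: "The total score ranges from 0 to 66", with entry restricted to "a baseline score of the Fugl-Meyer Assessment (FMA) of 20 to 60".
- mRS: "The mRS scores range from 0 to 5". The same section also defines a favourable outcome as a score of 2 or less.
- BBT: a count of blocks moved in 1 minute. The apparatus "contains 150 colored wooden cubes in a box with two compartments", but no total score is given.
- Activity monitors: "the amount of physical activity (counts/min), activity intensity, and energy expenditure in real life".
- SIS: 59 items, with no total or range.

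**The concern.** The fallback assumes that each outcome has a total score and that a tenth of it is a meaningful step. For some listed outcomes the first assumption fails, and for the mRS the second does. Whoever carries out the sentence must then supply a missing total or choose a cut-off. If that happens after the data are seen, the responder counts depend on the choice.

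A second weakness applies to any cut-off on a change score, whatever its source. The FMA stops at 66 and patients may enter at 60, so some eligible patients have little room to improve. An unadjusted chi-square takes no account of where a patient started.

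At stake is the meaning of the responder results, which the article presents as a further examination of efficacy.

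**Working it through.** The plan states no numeric MCID, so there is no figure to reproduce. The check applies the rule to each scale as the article describes it.

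**Step 1. The fallback, outcome by outcome.** Formula: cut-off = 0.10 × maximum score. Where scores are whole numbers, the working cut-off is the next whole number at or above it.

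| Outcome | Maximum from the article | 10% | Working cut-off |
|---|---|---|---|
| FMA | 66 | 6.6 | 7 |
| mRS | 5 | 0.5 | 1 grade |
| ABILHAND (raw) | 23 items × 2 = 46 | 4.6 | 5 |
| QMI | 35 items × 7 = 245 | 24.5 | 25 |
| FIM | 126 | 12.6 | 13 |
| BBT | none stated | not defined | not defined |
| SIS | none stated | not defined | not defined |
| Activity monitors | none exists | not defined | not defined |

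- *Activity monitors.* Counts per minute, intensity and energy expenditure have no total, so the rule has no value.
- *BBT.* If the 150 cubes were taken as the total, the cut-off would be 0.10 × 150 = 15 blocks. That total implies 60 s / 150 = 0.4 s per block. The article never calls 150 a total score, so this is only an illustration of the gap.
- *SIS.* Nothing can be computed from the article.
- *mRS.* Scores are whole grades, so the smallest possible change is 1, and 1 / 5 = 20% of the scale. Every patient who improves at all therefore reaches 0.5, and the nominal 10% acts as 20%.
- *FMA, ABILHAND, QMI, FIM.* The rule gives a usable number.

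**Step 2. The ceiling on the FMA.** A patient with baseline b can gain at most 66 − b, and cannot respond to a cut-off c if 66 − b < c.

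- At b = 60 the largest gain is 66 − 60 = 6, so the patient is a non-responder for any c above 6, even with a perfect final score.
- At c = 6.6 the condition is b > 59.4. Among whole-number baselines from 20 to 60, that is the score 60 only: one of 60 − 20 + 1 = 41 eligible scores.

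**Step 3. Where the result goes.** The responder counts enter the chi-square test only. The repeated-measures ANOVA uses the scores themselves and needs no MCID.

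**The case against.** The strongest reply is that the 10% rule is conditional. An established MCID comes first, and the article does not say which outcomes lack one. If all the outcomes in question have established values, the fallback never operates. Cut-off values are also normal content for an analysis plan, the article is a condensed text, and the responder analysis is introduced as an addition to the ANOVA.

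Much of this stands. Which outcomes are affected cannot be settled from the article, and the absence of the values themselves is no fault. What remains is that the rule is written down for the clinical outcomes generally and, where invoked, has no value for some of them. An analysis plan that follows the sentence inherits that.

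Four stronger readings are tempting and are not supported:

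- *The mRS cut-off is impossible.* A change of 0.5 cannot occur, but the test is whether the change reaches the cut-off, and one grade does. The rule works in practice as a change of at least one grade.
- *FMA baselines of 57 to 60 cannot respond.* That needs a cut-off of 10 (66 − 10 = 56), which the article does not give. It would also be an established value, not the fallback.
- *The lower power of a responder chi-square, compared with an F test on the scores, measures the harm of the 10% rule.* That loss is the general cost of dichotomising and would arise with a well-founded MCID too.
- *The responder test could decide the trial.* Nothing in the article gives it that role.

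**Conclusion.** The point holds in limited form. Of the eight clinical outcomes listed, the fallback has no value for one (activity monitors), lacks a stated total for two (BBT and SIS), and on a fourth (mRS) counts any one-grade improvement as response. For the other four it gives a usable cut-off. These are the consequences if the fallback is invoked; the article does not show that it will be for any particular outcome.

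The FMA ceiling is a separate and small matter. With the fallback value it touches only patients who enter at exactly 60, and how many there will be is unknown. It would apply equally to an established cut-off above 6. Because allocation is random and stratified by FMA severity, the ceiling should not favour one arm systematically; it mainly removes information.

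The assessment rests on the scale descriptions in the article and on whole-number scoring of the mRS and FMA. The primary FMA comparison by ANOVA is unaffected.

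**What to change.** Replace the fallback sentence with a short specification:

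1. Restrict the responder analysis to outcomes with a bounded score and one named cut-off, fixed before unblinding.
2. Analyse the activity monitors as continuous only. Do the same for the BBT and SIS if no cut-off is fixed for them.
3. For the mRS, use the article's own favourable-outcome definition (≤ 2).
4. Replace the unadjusted chi-square by logistic regression with treatment group and the baseline score of that outcome. This does not let a patient at FMA 60 reach a cut-off above 6, but the comparison then takes account of starting level.
5. Label the responder analysis as supportive of the ANOVA.

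The cost is a change of wording. The baseline scores are already collected, so no new data are needed. The small downside is fewer responder tables. The article reports recruitment as ongoing at submission; the change is useful only if made before unblinding.

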## Discussion

The study aim is to investigate the treatment efficacy and mechanisms of neural activity of AOT and MT and compare them with those of the control intervention for patients with stroke. AOT and MT are two novel and promising approaches for enhancement of stroke motor recovery through different afferent inputs and patterns of visual feedback. AOT focuses on the observation of actual actions of another person and execution of what is seen, whereas MT emphasizes observing the mirror reflection of arm movements in the non-affected arm, as if it were the affected one. AOT and MT aim to prime the motor system through the MNS for promoting neuroplasticity and motor function of stroke patients; however, their effectiveness in stroke rehabilitation is equivocal and warrants investigation.

While translating research evidence into clinical practice, patients can receive recommended rehabilitation care and therapy. After the study has been completed, and if positive results are achieved, we will provide scientific evidence of treatment effects and neural activity changes after AOT and MT. Based on the overall study results, our approaches might become new add-on features of modern neurorehabilitative treatments, and could potentially be used in rehabilitation settings. Future applications of AOT and MT may include telerehabilitation or home-based rehabilitation through web-based or video teaching.

## Trial status

At the time of submission, the recruitment of study participants is ongoing.

## Abbreviations

AOT: Action observation therapy
AROM: Active range of motion
BBT: Box and Block Test
FIM: Functional Independence Measure
FMA: Fugl-Meyer Assessment
MCID: Minimal clinically important difference
MEG: Magnetoencephalography
MNS: Mirror neuron system
mRS: Modified Rankin Scale
MT: Mirror therapy
QMI: Questionnaire Upon Mental Imagery
SIS: Stroke Impact Scale
UE: Upper extremity
